### Sample size calculation and randomisation

On the basis of a consensus within the study group, we determined the absolute improvement of the primary outcome measure of 25% between the intervention condition and the control condition on the primary outcome measure. We calculated sample size with a method that takes into account the intracluster correlation coefficient (ICC), the number of events, the expected effect, and the power of the study [17].

Our trial was designed with a limited number of cluster units (6 cluster units) able to participate. Using an assumed ICC of 0.05, which is a conservative assumption [18], an expected cluster size of 200 children, a worst case control rate of 50%, a two-sided alpha level of 0.05 and a power of 80%, 1289 children were needed to detect a 25% difference in rates between the two groups.

Following the baseline observation phase, the six clusters were randomly assigned to the intervention condition or to the control condition.

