**Methods/design:**

We carried out 1) a six-month observational phase focusing on the medical care procedures relative to malnourished children followed by 2) a cluster randomised controlled trial phase to evaluate the impact of a multidisciplinary nutrition team over an 18 month time frame.

Based on power analyses and assuming a conservative intracluster correlation coefficient, 1289 children were needed to detect a 25% difference in rates between the two groups of the cluster trial.

The implementation of our intervention was coordinated by the NST and had three major components: a) access to a computerised malnutrition screening system associated with an automatic alert system, b) an awareness campaign directed toward the health care workers and c) a leadership based strategy.

Main outcomes included the number of daily weighings during hospitalisation, the investigation of malnutrition etiology and the management of malnutrition by a dietician and/or the NST.

Due to the clustered nature of the data with children nested in departments, a generalized estimated equations approach will be used to analyse the impact of the multifaceted intervention on primary and secondary outcomes.

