## Discussion

### Discussion of study design

We chose to conduct a cluster randomised trial. This choice is justified with respect to the form of the intervention, which is carried out at the level of the clinical teams (through educational intervention and a computerised malnutrition alert system) and at the level of the dieticians (through a dashboard identifying malnourished children). The intervention was targeted at health care professionals with the aim of studying its impact on patient outcomes [21]. No intervention was performed at the patient level. Data were gathered at the patient level, which means that our analysis had to take two levels into account: the patient level and the cluster level.

Clusters were designed in order to carefully prevent healthcare workers form cross-ward contamination bias. Only a few large sized clusters were available for study (six clusters). This small number of clusters could result in a relatively high probability of chance imbalance between arms. Clusters from our single pool were randomly assigned to the intervention condition or to the control condition. This completely randomised design is most suited to trials in which large numbers of clusters are available for randomisation. We could have opted for a pre-stratification or matching according to baseline characteristics. We will take into account any differences in the characteristics of the children between the clusters within the statistical analysis, by adjusting the models according to the variables of interest.

We performed an observational baseline phase. For six months, prior to the randomised trial, we collected data pertaining to children presenting the inclusion criteria. This phase allowed us to better understand how the treatment of malnourished children was implemented in the departments participating in the study and to test the feasibility of child enrolment. It allowed us to enable calculation of the ICC of the clinical department data (which confirmed that we could retain our hypothesis of an ICC of 0.05). Moreover, it will allow additional statistical analyses comparing main outcome measures before and after implementation of the multifaceted intervention.

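### The stated 80% power is not available from six clusters: at the plan's own ICC of 0.05 it is about 54–56%, and no number of children lifts it above about 60%

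*Protocol article*

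**What the plan says.** The section Sample size calculation and randomisation fixes the target effect: "we determined the absolute improvement of the primary outcome measure of 25% between the intervention condition and the control condition". It then states the constraint on the design: "Our trial was designed with a limited number of cluster units (6 cluster units) able to participate". The remaining inputs are an ICC of 0.05, described as conservative, "an expected cluster size of 200 children", a worst-case control rate of 50%, and a two-sided alpha of 0.05. The conclusion is "a power of 80%, 1289 children were needed to detect a 25% difference in rates between the two groups". The abstract repeats that "1289 children were needed to detect a 25% difference in rates".

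The Discussion of study design returns to the ICC and says that the six-month baseline phase allowed it to be calculated, "which confirmed that we could retain our hypothesis of an ICC of 0.05". The same section acknowledges that six is a small number of clusters, but only as a risk of chance imbalance between arms.

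**The concern.** The inputs do not fit together. Six clusters of 200 give 1200 children, not 1289. The shortfall cannot be made up simply by enlarging the clusters, because the design effect rises with cluster size. Inflating an individually randomised sample size by the design effect also treats the between-cluster variance as known. With six clusters it is estimated on 6 − 2 = 4 degrees of freedom, and the power lost that way does not appear in the formula.

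The stated power is what readers will use to interpret the result. If it is too high, a non-significant result will be read as evidence against a 25-point improvement when the trial had little better than an even chance of detecting one.

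**Working it through.** **Inputs from the protocol article (Sample size calculation and randomisation).** Control rate 0.50; intervention rate 0.75 (25 points absolute); two-sided alpha 0.05; power 80%; ICC 0.05; cluster size m = 200; six clusters.

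**Assumptions.** Three clusters per arm and equal cluster sizes; the article states neither.

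**1. Reproducing 1289.**
- Pooled rate: (0.50 + 0.75)/2 = 0.625.
- n per arm = (1.960 + 0.842)² × 2 × 0.625 × 0.375 / 0.25² = 58.87.
- Design effect = 1 + 199 × 0.05 = 10.95.
- Total = 2 × 58.87 × 10.95 = 1289.2.

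The multiplication is correct, and it identifies the method: normal quantiles with pooled variance.

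**2. Clusters implied.** 1289/200 = 6.45, against six available.

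**3. Effect of larger clusters.** Effective sample size per arm is 3m / (1 + (m − 1) × 0.05).
- m = 200: 600/10.95 = 54.8.
- m = 1289/6 = 215: 55.1.
- m → ∞: 3/0.05 = 60.

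The plan's own formula needs 58.87 per arm. Solving for m gives 58.87 × 0.95 / (3 − 0.05 × 58.87) ≈ 987 per cluster, or about 5,900 children. This figure is sensitive to the variance used: with unpooled variance the requirement is 54.94 per arm, met at about 206 per cluster (about 1,240 children).

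**4. Power with six clusters.** The noncentrality is 0.25 / √(V × DE / (3m)). V is 0.46875 (pooled) or 0.4375 (unpooled), and DE is the design effect. The critical value of t on 4 df is 2.776, against 1.960 for the normal.

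| Children per cluster | Noncentrality (pooled / unpooled) | Power, normal | Power, t on 4 df |
|---|---|---|---|
| 200 | 2.70 / 2.80 | 77% / 80% | 53.6% / 56.3% |
| 215 | 2.71 / 2.81 | 77% / 80% | 53.8% / 56.5% |
| No limit | 2.83 / 2.93 | 81% / 83% | 57.2% / 59.9% |

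A beta-binomial simulation of a cluster-level t-test (200,000 runs) gave 56.1% at both 200 and 215 per cluster, and 59.3% in the limit. A 2 v 4 split gives 49–54% at 200 per cluster.

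**5. Detectable difference.** At 200 per cluster on 4 df, 80% power against a 50% control rate needs a difference of 33.8 points (pooled) or 32.0 points (unpooled).

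**6. Dependence on the ICC** (t on 4 df, 215 per cluster, pooled to unpooled):

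| ICC | Power |
|---|---|
| 0.02 | 85–87% |
| 0.03 | 72–75% |
| 0.05 | 54–57% |
| 0.10 | 32–34% |

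**7. What the baseline phase can say about the ICC.** The article gives no baseline estimate or sample size. As an illustration, take an estimate of exactly 0.05 and 200/3 ≈ 67 children per cluster (six months against eighteen). The ANOVA F ratio is 1 + 67 × 0.05/0.95 = 4.53 on 5 and 396 df. Its 95% limits translate to an ICC of about 0.01 to 0.28. Over that interval, power on 4 df runs from about 97% down to 15%.

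**The case against.** The strongest reply is that nothing has been miscalculated. The figure 1289 follows from its formula, 200 is only an expected cluster size, and on a normal basis six clusters give 77–80%. That is right as far as it goes: the step from 6.45 to 6 clusters costs 0–3 points, and nearly all of the loss comes from the 4 degrees of freedom. The 987-per-cluster figure likewise belongs to the pooled formula the plan used and should not be read as a general requirement.

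A second reply is that the planned analysis is not a t-test on 4 df. Data analysis of the cluster randomised trial specifies GEE with robust standard errors and a Wald test, and states no small-sample correction. If the Wald statistic is referred to the normal distribution, nominal power may be near 80%, but the test does not hold its level. With 3 v 3 equal clusters the uncorrected robust variance is 2/3 of the unbiased one, so the test rejects when |t| on 4 df exceeds 1.960 × √(2/3) = 1.60, which has probability about 18% under the null. That does not deliver 80% power at the stated two-sided 0.05. It does mean that, under such a test, false-positive findings are as much a hazard as a misread null.

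Third, the ceiling of about 60% holds at an ICC of 0.05; at 0.02 power exceeds 80%. This stands, and it is why power should be shown on both sides of 0.05. It does not rescue the claim, because 0.05 is the plan's own input, kept after the baseline phase. Covariate adjustment might recover some power, but the stated calculation takes no credit for it.

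Finally, the wording on the baseline ICC is a statement of retention rather than proof, and the interval in step 7 is illustrative. Even so, six clusters cannot confirm a value of 0.05 with useful precision.

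**Conclusion.** The concern holds. The arithmetic behind 1289 is correct, but the power attached to it is not a property of this design. At an ICC of 0.05, with three equal-sized clusters per arm and a test that keeps its two-sided 5% level, power for 50% versus 75% is about 54–56%. It cannot exceed about 57–60% however many children are included, and the 80%-power detectable difference is about 32–34 points. A 2 v 4 split lowers the power, and unequal cluster sizes generally would too. A lower true ICC would raise it. Neither Discussion passage on the small number of clusters corrects the claim: one mentions only chance imbalance, and the other presents GEE as preferable with few clusters per arm.

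**What to change.** Keep the sample and change the text.

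- In the abstract and in Sample size calculation and randomisation, replace the 80% claim. State that with six clusters of about 200 children and an ICC of 0.05, power for 50% versus 75% is about 55% (t on 4 df), and that the difference detectable with 80% power is about 32–34 points.
- State the assumptions alongside: the allocation of clusters to arms, equal cluster sizes, and a test that holds its two-sided 5% level.
- Show power at ICCs below and above 0.05, for example 0.02, 0.03 and 0.10.
- Drop the description of the ICC as conservative and, in the Discussion of study design, as confirmed. Give instead the baseline estimate with its confidence interval and the power across that interval.

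The cost is a less favourable stated power. No new data are needed, and the sample does not change.

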### Blinding

Health care providers, participants and researchers were not blinded to group allocation.

## Ethical approval and informed consent

Approval for the study was obtained from the Sud Est III Institutional Review Board (study identifier: 2008–036 B) and from the French Data Protection Agency (CNIL).

As the promoter of this biomedical research, which falls within the scope of French Law n°2004-806 of 9 August 2004, the Hospices Civils de Lyon has acquired liability insurance coverage and stood as guarantors of the proper execution of the study.

Cluster leaders gave consent to the trial on behalf on the potential cluster members. Consent was sought before the observation phase and randomisation.

The parents of the children were informed of the study through an information sheet supplied with the patient welcome leaflet provided for each parent at the time their child is hospitalised. Parental written consent was not required in the context of this study [19]. In the event of a refusal to participate in the sharing of hospitalisation data for this study, the head of the hospital department was to record this information in the child’s medical file. Children could be withdrawn from sharing hospitalisation data but not from the intervention.

### Data analysis of the cluster randomised trial

All statistical analyses will be performed in Statistical Analysis System (SAS®) software version 9.2 (SAS Institute, Cary, NC). Analyses will be performed according to the intention-to-treat principle. All malnourished children screened in all clusters allocated to the intervention or control arm will be included in the analysis. In the event of multiple hospitalisations for the same patient, only the first stay of the study period will be retained.

Baseline characteristics will be summarised by pre- and post-intervention period and treatment group using frequency (percentage) for categorical variables and means (standard deviation) for continuous variables.

Clustering will be taken into account: a generalized estimated equations (GEE) approach will be used to analyse the impact of the multifaceted intervention on primary and secondary outcomes [20]. A GEE Poisson regression model will be performed for count data (as number of daily weighings) and GEE logistic regression models for binary variables (as investigation of malnutrition etiology, management by dietician, nutritional supplementation, complication occurrence during hospitalisation). The paediatric departments will be entered as the clustering variable into each model. For the GEE Poisson, the length of stay will be used as an offset. An exchangeable correlation matrix will be specified to account for potential within-cluster homogeneity in outcomes: all pairwise correlations among children within departments are the same. Robust estimates of the standard errors will be obtained which ensures, provided the model is correct, that the estimates are consistent even if the working correlation matrix is not correct. The impact of the multifaceted intervention will be adjusted for individual level characteristics included age, severity of malnutrition, comorbidities occurrence, complications occurrence and length of hospital stay after controlling for the collinearity between covariables. A Wald statistic will be used to test the significance of each coefficient in the model. The intervention effect will be expressed as adjusted odds ratio with its 95% confidence interval. GEE regression models will be fit using the SAS PROC GENMOD. Corresponding overall intra cluster correlation (ICC) coefficient was also estimated from GEE method using the CORRW option from the SAS PROC GENMOD.

For each arm, comparison of outcome changes between pre- and post-intervention periods will be computed using a GEE regression model, integrating the clustering of children by department. The period following intervention start will be the predictor, while all the potential confounders listed above will be considered in the final model based on a propensity score weighting approach. Immediate change and quarterly trend in clinical practices following the implementation of intervention will be also estimated.

All statistical tests were two-sided with p-value less than 0.05 regarded as significant.

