**Population at patient level**	
*Inclusion criteria*	Age 1 month to 18 years old
	Children recorded as malnourished based on their weight/height and height/age ratios upon hospital entrance, according to the Algoped nutritional risk score
*Exclusion criteria*	Age under one month, liver or kidney abnormalities, severe heart failure
	First weight recorded more than 2 days after admission, first height recorded more than 15 days after admission
	Stay less than 2 days

Head physicians of all eligible departments were contacted and invited to participate. All medical and surgical departments providing acute care in this paediatric university hospital participated in the trial (*i.e.*, 8 departments, 393 acute care beds (207 in medicine and 59 in surgery) performing 29 518 stays a year) except neonatal, intensive care and emergency units. Approximately 300 professionals were targeted (55 physicians and medical residents, 115 nurses, 12 dieticians, 100 paediatric auxiliary nurses and 27 physiotherapists).

Some nursing teams work across several departments. As a consequence, because our intervention targeted the practices of health care professionals, we grouped the relevant departments together into clusters in order to minimise contamination bias between departments. A total of six clusters were determined.

According to the French paediatric guidelines for the screening and treatment of malnutrition, the Algoped nutritional risk score was employed for assessing the nutritional status of every child based on weight and height measured at admission by health care workers [11]. Detection of malnourished children was based on the combined interpretation of two ratios. First, in order to detect acute malnutrition (stunting), the weight/height ratio (W/H) was calculated by dividing the child’s observed weight by the expected weight related to their observed height [14]. Second, in order to detect chronic malnutrition (wasting), the height/age ratio (H/A) was calculated by dividing the child’s observed height by the expected height related to their age. In cases of W/H > 90% and/or H/A > 94%, there was considered to be no malnutrition in the patient. In cases of W/H 80-90% and/or H/A 85-94%, there was moderate malnutrition, while W/H < 80% and/or H/A < 85% indicated severe malnutrition [15,16].

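### The GEE models cluster on departments, but the randomised units are six groups of departments; the cost depends on a correlation the article does not give

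*Protocol article*

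**What the plan says.** The Participants section keeps departments and clusters apart. It counts "8 departments, 393 acute care beds" and then explains the grouping: "Some nursing teams work across several departments", and so "we grouped the relevant departments together into clusters in order to minimise contamination bias between departments". The result is that "A total of six clusters were determined".

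The section on sample size and randomisation makes these groups the randomised units: "the six clusters were randomly assigned to the intervention condition or to the control condition". The Time frame section repeats that six clusters were randomised.

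The section on data analysis of the cluster randomised trial names a different unit: "The paediatric departments will be entered as the clustering variable into each model". The exchangeable working correlation is explained in the same terms: "all pairwise correlations among children within departments are the same". The models comparing periods within each arm are also described as "integrating the clustering of children by department". The Abstract and the discussion of study design likewise describe children as nested in departments. The article nowhere defines a model level for the six randomised groups.

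**The concern.** GEE takes different values of the clustering variable as independent. Two departments in one randomised cluster receive the same allocation by design and, by the article's own reason for merging them, may share nurses. The primary outcomes measure staff practice, and weighing is nursing work, so some correlation between merged departments is plausible. Clustering on department sets that correlation to zero.

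The sandwich variance protects against a wrong correlation structure inside the declared cluster. It does not protect against a cluster declared too small, so the article's remark about robust standard errors does not cover this case.

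The ICC is affected too. The model output would give a department ICC, and the discussion of study design says the assumed 0.05 was checked on department data. The sample size needs the ICC of the randomised unit. Every GEE model for primary and secondary outcomes inherits the problem.

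**Working it through.** **1. Which unit the sample size uses.** Inputs from the sample size section: control rate 50%, absolute difference 25 points (50% versus 75%, mean 0.625), two-sided alpha 0.05, power 80%, ICC 0.05, cluster size 200.

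- Per arm before clustering: 2 × 0.625 × 0.375 × (1.960 + 0.842)² / 0.25² = 58.87
- Design effect: 1 + (200 − 1) × 0.05 = 10.95
- Total: 2 × 58.87 × 10.95 = 1289.2

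This reproduces the stated 1289. Since 1289 / 200 = 6.4, the calculation fits the six randomised clusters. Eight departments would average 1289 / 8 = 161 children.

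**2. Hand check of the variance.** Let σ² be the between-department variance and r the fraction of it common to departments in one cluster. Assume four equal departments per arm, two of them in one cluster, and ignore binomial noise.

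- True variance of an arm mean: σ²(4 + 2r) / 16
- Expected department-level sandwich: σ²[4 − (4 + 2r)/4] / 16 = σ²(3 − r/2) / 16
- Ratio of true to estimated: (4 + 2r) / (3 − r/2), which is 1.33 at r = 0, 1.82 at r = 0.5 and 2.40 at r = 1

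The usual small-sample factor of 4/3 removes the shortfall at r = 0 but leaves 1.82 / 1.33 = 1.36 at r = 0.5 and 2.40 / 1.33 = 1.80 at r = 1. On the six clusters at r = 1, the true variance is σ²/3 and the expected sandwich 2σ²/9. The ratio is 1.50, and the factor 3/2 removes it completely. So the unit error is separate from the small-sample problem when sharing is material. With no sharing, the department sandwich falls less short than the cluster sandwich does at full sharing (1.33 against 1.50).

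**3. Simulated type I error.** Assumptions: three clusters per arm, one of them with two departments; ICC 0.05; both arms at 50%; about 1289 children; no covariates; exchangeable weights with sandwich variance. Department sizes were either 107, 107, 215 and 215 per arm or 161 each (100,000 replicates). The t versions rescale the sandwich by k/(k − 2), with k units in total, and use 6 df for departments and 4 df for clusters.

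| Share of effect common to merged departments | Wald z, departments | Wald z, six clusters | t, departments | t, six clusters |
|---|---|---|---|---|
| All | 24–26% | 18–19% | 11–12% | 5% |
| Half | 19% | 18–19% | 8% | 5% |
| Quarter | 16–17% | 18–19% | 6% | 5% |
| None | 14% | 18–19% | 5% | 5% |

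A different layout, with one cluster of three departments and five single departments, gives Wald z on departments of 24–25%, 20% and 15–16% for all, half and none, against 18–19% on the six clusters. With a t reference, departments give 11–13%, 8–9% and about 6%.

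**The case against.** The strongest reply is that *department* is loose wording for *cluster*. The analysis section mixes both terms in its sentence on the working correlation. The discussion of study design says the analysis has a patient level and a cluster level, and it defends GEE by the small number of clusters per arm. This has some force: the authors may intend six units. But the Participants section gives the two terms different counts, the instruction for the models names departments, and an analyst who follows it would code eight units. If only the wording is at fault, it still needs correcting.

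The second reply concerns size, and most of it stands.

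- A reader might infer that clustering on departments always makes the planned test more liberal. It does not: below roughly half sharing, the planned z test rejects less often on departments than on six clusters.
- A reader might attribute the whole 24–26% to the wrong unit. About 18% is already there with the right unit and comes from an uncorrected Wald test on six clusters.
- A reader might cite a rise in degrees of freedom from 4 to 6. The article specifies a Wald statistic and no t reference, so this bears only on a corrected analysis.
- A reader might say the grouping was made to handle correlated outcomes. The stated purpose is to limit contamination; correlation through shared nurses is a plausible consequence that the article neither states nor quantifies.

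**Conclusion.** As written, the unit of analysis is not the unit of randomisation, and the passages must be reconciled. That follows from the text alone. Its numerical effect does not, because the article gives neither the mapping of departments to clusters nor the correlation between merged departments.

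Under the assumed layout and ICC 0.05, moving from the six clusters to departments changes the type I error of the planned test by between about +7 points (full sharing) and about −4 points (none). With a t reference, the department analysis has 11–12%, 8% or 5% at full, half or no sharing, against 5% on the six clusters. A small-sample correction applied to departments therefore does not restore the nominal level unless sharing is negligible. The article does not support a claim that the trial's error rate is inflated by a known amount for this reason. Using the six clusters is necessary for a test that is valid whatever the sharing, but it is not sufficient.

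**What to change.** Replace the sentence on the clustering variable with: *The six randomised clusters will be the clustering (subject) variable in every model; department may enter only as a level nested within cluster. The ICC will be reported for the six clusters.* Bring the description of the working correlation, the models comparing periods, the Abstract and the discussion of study design into line, and state which departments form each cluster.

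In the same change, specify a small-sample reference for six clusters, for example a cluster-level t test on 4 df or a bias-corrected sandwich variance with a t reference. Changing the unit alone leaves about 18% type I error.

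In code this is one variable and one choice of test. The statistical cost is wider intervals: the two-sided 5% critical value is 2.78 on 4 df, against 1.96 for z. With six clusters of 1289 / 6 = 215 children, the design effect is 1 + 213.8 × 0.05 = 11.69 and the standard error √(2 × 0.625 × 0.375 × 11.69 / 644.5) = 0.092, so 0.25 / 0.092 is about 2.71. Power is then about 77% by the z approximation and about 54% by a t test on 4 df. That loss reflects having only six clusters; analysing departments would hide it, not remove it.

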Due to the clustered nature of the data with children nested in departments, a GEE approach will be used to analyse the impact of the multifaceted intervention on primary and secondary outcomes [20]. The characteristics and the health status of children in the same departments may be correlated, thus violating the independence assumptions of traditional regression models. In cluster randomized trials, standard methods for statistical analysis do not apply otherwise it will lead to underpowered studies and it will tend to bias observed p-values downward [22]. The GEE approach is also preferable rather than the random-effect regression models when testing the effects of cluster-level covariates (like the multifaceted intervention which is our only cluster-level exposure variable) [23], and when studying small number of clusters per arm.

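### Uncorrected robust standard errors and a Wald test on six randomised clusters give a nominal 5% test a type I error of roughly 14–25%

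*Protocol article*

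**What the plan says.** In the protocol article, *Sample size calculation and randomisation* states "Our trial was designed with a limited number of cluster units (6 cluster units) able to participate", and that after the baseline phase "the six clusters were randomly assigned to the intervention condition or to the control condition". The split between arms is not given. *Participants* explains that eight departments were grouped into these six clusters because some nursing teams work across departments.

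*Data analysis of the cluster randomised trial* fixes the inference: GEE logistic and Poisson models with an exchangeable working correlation, fitted in PROC GENMOD, with departments as the clustering variable. On the variance it says "Robust estimates of the standard errors will be obtained which ensures, provided the model is correct, that the estimates are consistent". The article adds that this protects against a misspecified working correlation. On the test it says "A Wald statistic will be used to test the significance of each coefficient in the model". Significance is two-sided p < 0.05. The same section plans within-arm pre/post GEE models.

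*Discussion of study design* treats the small number of clusters as a risk of chance imbalance. It also prefers GEE to random-effects regression when testing cluster-level covariates "and when studying small number of clusters per arm".

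**The concern.** The sandwich variance estimates between-cluster variability from the observed cluster residuals. With three clusters per arm it has two independent residuals per arm and is biased downwards. A Wald statistic with no stated degrees of freedom, read here as referred to the normal or chi-square distribution, also ignores that only 6 − 2 = 4 degrees of freedom exist between clusters. Both errors favour rejection, and neither a larger number of children nor child-level covariate adjustment adds between-cluster degrees of freedom.

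This is the trial's main comparison. If the intervention had no effect, each primary outcome would be declared significant several times more often than the stated 5%, and the 95% intervals would cover less often than claimed. The remark in the Discussion may lead a reader to believe that the method already deals with few clusters.

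**Working it through.** **Inputs from the article.** Six clusters; ICC 0.05; expected cluster size 200; control rate 50%; absolute difference 25 points (50% v 75%); two-sided alpha 0.05; power 80%; 1289 children; eight departments as the GEE clustering variable.

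**Assumptions.** The split (3:3, with 4:2 as an alternative), the actual cluster sizes, and which departments share a cluster are not stated.

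**1. The plan's own figure.** Design effect = 1 + (200 − 1) × 0.05 = 10.95. Per arm before inflation, with mean rate 0.625: (1.960 + 0.842)² × 2 × 0.625 × 0.375 / 0.25² = 58.87. Total = 2 × 58.87 × 10.95 = 1289.2. The stated 1289 is reproduced. This formula uses normal quantiles, with no allowance for 4 df.

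**2. Type I error, six equal clusters, 3:3.** With k = 3 clusters per arm, the uncorrected sandwich variance is (k − 1)/k = 2/3 of the unbiased variance. Rejecting at |z| > 1.96 is therefore rejecting at |t₄| > 1.96 × √(2/3) = 1.600, and 2 × P(t₄ > 1.600) = 18.5%.

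**3. Other configurations.**

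| Setting | Type I error |
|---|---|
| 3:3 equal, formula | 18.5% |
| Simulated logistic GEE, 6 × 215, ICC 0.01–0.10 | 18.0–18.5% |
| Simulated Poisson GEE with length-of-stay offset (assumed between-cluster SD 0.25 on the log scale) | 20.8% |
| 3:3, unequal sizes (assumed 60, 100, 150, 200, 300, 479), ICC 0.10 to 0.01 | 19.0–24.6% |
| 4:2 split | about 23% |
| Eight independent departments, 4:4: 2 × P(t₆ > 1.96 × √(3/4) = 1.697) | 14.1% |
| Eight departments, grouped ones sharing their cluster's effect (two clusters of two departments assumed), ICC 0.01–0.10 | 20.5–24.7% |

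Clustering on departments lowers the error only if departments within a randomised cluster are independent. The article's reason for grouping them, shared nursing teams, points the other way.

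**4. Half-measures (3:3, equal clusters).** Uncorrected variance with the t₄ critical value 2.776: 2 × P(t₄ > 2.776 × √(2/3)) = 8.6%. Unbiased variance with 1.96: 2 × P(t₄ > 1.96) = 12.2%. Both parts must be corrected.

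**5. Full corrections (3:3, equal clusters).** A cluster-level t test on 4 df gives 5.0%. Kauermann-Carroll multiplies the sandwich variance by 3/2, which makes it unbiased here, so with t₄ it also gives 5.0%. Mancl-DeRouen multiplies by 3/2 once more, so with t₄ it gives 2 × P(t₄ > 2.776 × √1.5) = 2.7%. The corrections are not interchangeable.

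**6. Cost in precision and power.** Interval width ratio = 2.776 × √1.5 / 1.96 = 1.73. For power, 1289/6 = 214.8 children per cluster and the design effect is 1 + 213.8 × 0.05 = 11.69. The variance of a cluster proportion is 0.25 × 11.69/214.8 = 0.01361 at 50% and 0.1875 × 11.69/214.8 = 0.01020 at 75%. SE = √[(0.01361 + 0.01020)/3] = 0.0891, so the non-centrality is 0.25/0.0891 = 2.81. Power is 80% with a normal reference, about 57% with t₄, and about 41% with Mancl-DeRouen and t₄.

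**The case against.** **The size is not one number.** A reader might infer that the planned test has an 18% error rate. That figure needs a 3:3 split, roughly equal clusters and GEE clustering on the six randomised units. The article gives neither split nor sizes, and it clusters on departments. This objection stands, and only a range can be supported. Its lower end is still nearly three times nominal. The calculations also omit the full planned covariate list, so they are approximations to the fitted model.

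**The Discussion remark.** A reader might infer that the article claims uncorrected GEE is valid with few clusters. It does not. The sentence compares GEE with random-effects models only, and nothing here tests that comparison or shows it to be false. What remains is that the remark reassures by citing few clusters per arm in favour of GEE without saying that a small-sample correction is then needed.

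**An unseen analysis plan might add a correction.** That is possible, since a journal article is condensed. But the article is not silent: it names the variance estimator, the test, the procedure and the significance level. As written, these do not deliver 5%.

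**Results.** A reader might also infer that any positive finding would be an artefact. The documents contain no results. The point is that the planned p-values could not distinguish the two cases at the stated error rate.

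**Conclusion.** The point holds as a statement about the planned inference: robust standard errors with a Wald test and no small-sample correction are unsuitable for six randomised clusters. The type I error of the nominal 5% test is roughly 14–25% over the splits, cluster sizes and clustering units examined, all of which are assumptions because the article does not state them. It affects all between-arm p-values and 95% confidence intervals for primary and secondary outcomes. The excess over 5% does not depend on any single assumption. The Discussion sentence is incomplete, not shown to be wrong. The primary inference should be changed before results are reported.

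**What to change.** 1. Use the six randomised clusters, not departments, as the GEE clustering unit.
2. Name one primary method. A suitable choice is GEE with the Kauermann-Carroll corrected variance and a t reference on 4 df, which keeps the planned adjusted odds ratio. Give a cluster-level t test on 4 df as sensitivity analysis. One method must be fixed because *Time frame* says the data are gathered and analysis is underway, so a menu of corrections would leave room for choice after the fact.
3. Check the chosen method by simulation at the actual cluster sizes. The exact 5.0% holds for equal clusters. With the unequal sizes assumed above, uncorrected variance with t₄ gave 9.5–13.7% and Mancl-DeRouen with t₄ gave 3.5–3.9%. Kauermann-Carroll lies between them, so it may exceed 5% under strong imbalance.
4. Do not rely on a permutation test alone: a 3:3 split has 20 allocations, so the smallest two-sided p is 2/20 = 0.10.
5. Apply the same kind of correction to the within-arm pre/post models, with correspondingly fewer df, or label them descriptive.
6. Qualify the Discussion sentence by adding that GEE with few clusters needs a small-sample correction.

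The change needs no new data, only revised text and code. The cost is intervals about 1.7 times as wide (3:3 split) and power of about 57% on 4 df for 50% v 75% with 1289 children at ICC 0.05. The report should state that figure beside the planned 80%.
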